## Abstract

**Background:**

In China, about 53.4 million women (11%) have type 2 diabetes (T2DM). Women with prior 2 (GDM) are at a high risk for T2DM. Postpartum lifestyle interventions have been effective in reducing T2DM for this population, but the evidence is limited to interventions provided in urban areas, despite the fact that a higher prevalence of undiagnosed T2DM was found in rural areas in China. The primary purpose of this proposed study is to examine the effect of a postpartum intensive lifestyle modification (ILSM) program on physiological health outcomes (T2DM development, insulin resistance, and weight-related variables), weight-related health behaviors (dietary intake and physical activity), and psychosocial outcomes (self-efficacy, perceived stress, social support, and health-related quality of life) compared to usual care at 3, 6, and 18 months post baseline assessment. The secondary outcomes are to identify potential mediators and moderators on change of physiological health outcomes.

**Methods/design:**

A multi-site randomized clinical trial (RCT) will be conducted to examine the efficacy of an evidence-based Intensive Lifestyle Modification (ILSM) program compared with usual care for women with prior GDM living in rural areas in China. A total sample of 256 participants will be recruited in the study. The intervention consists of six bi-weekly in-person group sessions, five bi-weekly telephone consultation sessions, and three monthly telephone consultations to encourage behavior change. The usual care provided to the control group will utilize current clinical guideline and recommendations for T2DM prevention. Outcome measures include physiological variables (OGTT-2 h, HbA1c, weight, and waist circumference); weight-related health behavioral (dietary intake and physical activities); and psychosocial variables (self-efficacy and social support) at 3-, 6- and 18- month after baseline. We will also assess the potential cost-effectiveness of ILSM (net cost per T2DM case and per DALY averted) compared with usual care.

**Discussion:**

If successful, this ILSM program can be adapted and used in rural areas as a blueprint for clinical guidelines to decrease T2DM by improving postpartum GDM care in China. Findings of this study are expected to make a significant contribution to public health practice and health policy related to T2DM prevention in China.

**Trial registration:**

Chinese Clinical Trial Registry, ChiCTR1800015023. Registered 1 March 2018 - Retrospectively registered, http://apps.who.int/trialsearch/default.aspx.

## Background

Type 2 Diabetes Mellitus (T2DM) is a global health concern especially in low- and middle-income countries, which constitute 77% of all cases of diabetes. China is also experiencing this global health epidemic because China has the largest diabetic population in the world (about 114 million adults or one in 4 adults) [1, 2] and the overall disease burden of diabetes is huge (19.12 DALYs per 1000 population in 2010) [3]. However, health disparities are seen in rural areas as undiagnosed T2DM prevalence is higher in rural than urban areas in China (70.5% vs. 58.0%), possibly due to lack of awareness of T2DM and access to high quality health programs in rural areas [4]. Thus, efforts to prevent T2DM and effective intervention to prevent T2DM in rural areas are essential in China.

Risk factors associated with T2DM include women with Gestational diabetes mellitus who lives in rural area [5]. Gestational diabetes mellitus (GDM) is defined as any degree of glucose intolerance with onset during pregnancy [6]. The prevalence of GDM is 18.9% in China [7]. For mothers with prior GDM, the overall risk of developing T2DM is over seven-fold higher than those who had normal glyceaemic pregnancies [8]. The incidence of T2DM in 1–10 years after a diagnosis of GDM ranges from 10 to 40% [9], with up to 70% of women developing T2DM within 20 years, depending on race/ethnicity [10]. Because of the recent family planning policy change in China, many women will have more than one child during child bearing age and repeated exposure of GDM (diagnosis of GDM in more than one pregnancy) will significantly increase women’s risk for T2DM [7]. In addition, residents in rural areas are largely unaware of their T2DM risk [4] and health care program for women with prior GDM is absent despite the high rate of undiagnosed T2DM in rural areas [11], an intervention program tailored to this high risk group will be the first step for changing clinical practice and policy development aimed to decrease health inequity in China.

Many interventions, including lifestyle and pharmacotherapy interventions, have been developed to prevent T2DM. Lifestyle interventions, in particular, have demonstrated potential efficacy in reducing T2DM incidence and may be superior to pharmacological retreatment [12]. A recent systematic review [11] examined the efficacy of lifestyle interventions in decreasing T2DM for women with GDM using randomized clinical trials found that the majority of the trials (92%) targeted women in an urban setting [13–23] and the results suggest that postpartum lifestyle interventions for women with GDM history can decrease T2DM risk significantly on the short-term follow up. However, these studies are limited to pilot or feasibility studies and only three studies were conducted in China and all of them focused on women in urban cities [15, 16, 21].

Although about half of the population (700 million people) resides in rural areas in China [24], there is a huge rural-urban gap of income, education and health resources, with the living situation in urban areas being much better than that in the rural areas [25]. People in rural areas are also suffering from unhealthy lifestyle practices as they are more likely to smoke, exercise less frequently, and have lower health literacy than their urban counterparts [26, 27].

Women living in rural area in China practice more traditional Chinese customs of a “sitting month” during postpartum period that include more sedentary behavior and increased consumption of high-calories, high-fat, and high-protein food intake during the first month [28]. These traditional practices might make Chinese women miss the optimal period for weight loss and healthy lifestyle change [29]. Other issues could increase risk for T2DM in women in rural areas include inadequate in-service training, staff shortages, poor resource distribution, and transportation difficulties which create health inequality in rural areas in China [30]. Thus, diabetes prevention interventions with lifestyle modification for rural Chinese women with prior GDM are urgently needed.

The primary purpose of this proposed study is to examine the effect of a postpartum intensive lifestyle modification (ILSM) program on physiological health outcomes (T2DM development, insulin resistance, and weight-related variables), weight-related health behaviors (dietary intake and physical activity), and psychosocial outcomes (self-efficacy, perceived stress, social support, and health-related quality of life)compared to usual care at 3, 6, and 18 months post baseline assessment. The secondary outcomes are to identify potential mediators and moderators on change of physiological health outcomes. This paper describes the development of this culturally sensitive ILSM program and study procedure.

### Study participants

Participants will be invited to participate in this study if they meet the following inclusion criteria: 1) Women with a history of GDM; 18 years or older; 2) at least six weeks post-partum at the beginning of the study; 3) intend to live in the research counties for at least 3 years; 3) intend to seek primary maternal and child health care in the research sites for at least 3 years; 4) have telephone-access either from family members, friends, or neighbors; 5) be able to speak Chinese.

Exclusion criteria: 1) Planning to become pregnant within the next three years; 2) Currently pregnant; 3) Diabetes diagnosed before pregnancy or after delivery; 4) Medications that influence glucose metabolism; 5) Multiple pregnancies (three or more); 6) Physical or cognitive disability; 7) Current addictive drug abuse; 8) Severe psychiatric disorders.

The power calculations for multivariate procedures are generally more complex and require a priori assumptions that are difficult to verify. Using GPower3.1 we calculated the power of tests of odds ratios in logistic regressions comparing threshold values of OGTT 2 h and HbA1c in ILSM versus control samples. For odds ratios of 0.667 (odds of insulin resistance above threshold in the ILSM groups versus the equal odds in the control group), a combined sample of *N* = 256, relatively high correlations between the other covariates, and a probability of a Type 1 error of .05, the power of the test against null hypothesis of that the odds ratio is 1.0 is about 0.71.

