### Recruitment

Recruitment of potential participants will occur by a review of medical records of the women who delivered babies in the research sites. Potential participants who meet inclusion criteria will receive a phone call from a trained project field officer to explain the purpose of the study and assess interest in participation. The trained project field officers who are physicians or nurses working in the research sites will be recruited from the research sites.

The project field officers will confirm their eligibility and obtain consent. As part of eligibility assessment, all interested study participants will undergo postpartum HbA1c testing to make sure the potential subjects do not have T2DM. If HbA1c suggests T2DM, the participant will not be eligible to participate in the study. However, she will be referred to the physicians for further T2DM diagnosis and treatment. If HbA1c are within normal limits, the women will be recruited. Women who do not meet the inclusion criteria will be thanked for their time. We will also document reasons from mothers who decline to participate in the study.

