### Variables and measurements

Each measure was selected to operationalize theoretical constructs and has been used in Chinese rural populations and demonstrated adequate psychometric properties. The research team will measure outcomes at baseline (T-0), immediately after main ILSM at 3 months (T-1), immediately post intervention at 6 months (T-2) and 18-month post intervention (T-3), which are displayed in Table 3. All measures employed in the proposed study will be collected by trained research assistants who are blinded to the group assignments.

**Table 3 Tab3:** Variables and measures collected at evaluation time points

Variables		Data source	Measures	Time point			
				T-0	T-1	T-2	T-3
Covariates	Socio-demographic factors	Survey & medical record	Age, marital status, education level, occupation, annual household income, and ethnicity.	×			
	Health characteristics		Smoking status, alcohol consumption, pre-pregnancy BMI, gestational weight gain, parental history of diabetes, GDM, and cardiovascular disease.	×			
	Clinical characteristics		Gestational week and age at the diagnosis of GDM, numbers of pregnancies, history of pregnancy complications, birth weight of children, gestation week at delivery, treatment for GDM.	×			
Weight-related Behaviors	Dietary intake	Survey	Food frequency questionnaire [40]	×	×	×	×
	Physical activities		International Physical Activity Questionnaire (Short version) [41]	×	×	×	×
Psychosocial Variables	Self-efficacy: the belief in one’s effectiveness in performing specific tasks.	Survey	Self-rated abilities for health practices scale [42]	×	×	×	×
	Perceived stress: the feelings or thoughts that an individual has about how much stress they are under over a given time period.		Perceived Stress Scale [43]	×	×	×	×
	Social support: the perception and actuality that one is cared for.		Social Support Rating Scale [44]	×	×	×	×
	Quality of life: the general well-being of individuals		The World Health Organization Quality of Life Scale-BREF [45]	×	×	×	×
Physiological outcomes	Insulin resistance: a physiological condition in which cells fail to respond to the normal actions of the hormone insulin	Spot measuring	OGTT-2 h	×	×	×	×
	T2DM screening & development		HbA1c ≥6.5% is considered T2DM.				
Weight-related measures	BMI & Waist circumference	Spot measuring	BMI is weight/height^2^ (Kg/m^2^)	×	×	×	×
Cardiovascular disease risk	Blood Pressure	Spot measuring	Systolic blood pressure, Diastolic blood pressure	×	×	×	×

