### Statistical analysis

Our analysis plan focuses on comparisons between ILSM and control groups with respect to key intermediate outcomes: HbA1c (%),OGTT 2 h (mmol/L), BMI, waist circumference (in cm), SBP and DBP (mmHg), and measures of dietary intake, physical activity, self-efficacy, and social support. The comparisons take the form of 1) simple differences of average values of change (for quantitative characteristics) from baseline to follow-up measures or turnover tables showing baseline versus follow-up (for data organized into categories) and 2) more complex analyses based on multivariate methods that incorporate adjustment for clustering and covariates.

We will assess cost-effectiveness using an existing spreadsheet-based simulation model called GeDiForCE (Gestational Diabetes Formulas for Cost-Effectiveness), developed by UCSF and Health Strategies International with funding from NovoNordisk. This model uses a decision tree and input values from published studies to portray the risks of T2DM with and without a post-partum intervention. In this study, we will adjust input values to reflect data collected on costs and effectiveness. The cost data described above can be directly incorporated into the model. The effectiveness data will be calculated from the clinical and physiological outcomes above. We will directly incorporate incidence of T2DM. However, due to the relatively short follow-up time frame, as compared with a delay of ten or more years for the incidence of T2DM, we will also use short-term changes in physiological indicators (such as OGTT-2 h and HbA1c) in a simple risk-of-progression model in order to predict long-term effects on incidence of T2DM. This progression model will be calibrated to empirical evidence on the progression from glucose intolerance to T2DM.

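### One power figure (about 0.71) is given for thresholds of both OGTT-2 h and HbA1c, with no cut-off or control rate for either; it cannot hold for HbA1c ≥6.5%, a level excluded at entry

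*Protocol article*

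**What the plan says.** In the protocol article, the power paragraph (end of Study participants) describes logistic regressions "comparing threshold values of OGTT 2 h and HbA1c in ILSM versus control samples". The effect is an odds ratio of 0.667, explained as "odds of insulin resistance above threshold in the ILSM groups versus the equal odds in the control group". With N = 256, a type 1 error of 0.05 and unquantified but fairly high covariate correlations, it reports a power of about 0.71. It gives no cut-off for either measure and no control proportion as a number.

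Five other places bear on the HbA1c part:

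- Table 3 (Variables and measurements): "HbA1c ≥6.5% is considered T2DM". This is the only HbA1c cut-off in the article.
- Recruitment: "If HbA1c suggests T2DM, the participant will not be eligible to participate in the study". Women with HbA1c in the normal range are enrolled.
- Background: "The incidence of T2DM in 1–10 years after a diagnosis of GDM ranges from 10 to 40" per cent.
- Statistical analysis: T2DM incidence is to be supplemented by a progression model "due to the relatively short follow-up time frame, as compared with a delay of ten or more years for the incidence of T2DM".
- Variables and measurements, text after Table 3: HbA1c is one of three primary outcome measures, with BMI and OGTT-2 h.

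**The concern.** For a binary outcome the control proportion p sets the information in the trial through p(1 − p), which is largest at p = 0.5. Even odds is therefore close to the most favourable input available. It may suit some cut-off of OGTT-2 h, but it does not suit HbA1c ≥6.5% in a cohort where nobody starts at that level. There the proportion above threshold at follow-up consists only of new cases, which the article itself expects to be few within the trial.

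HbA1c is a primary outcome and the measure of T2DM development, and no other power is stated for it. A reader would credit the diabetes comparison with about 71% power when the design has far less.

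**Working it through.** **Inputs.** From the article: odds ratio (OR) 0.667, N = 256, alpha 0.05, final assessment 18 months after baseline. Assumed: 128 per arm, two-sided test, no loss for clustering, dropout or covariate correlation. ln(0.667) = −0.405.

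**1. The stated figure.** Control odds of 1 give p0 = 0.50, and p1 = 0.667/1.667 = 0.400. For the Wald test of the log odds ratio,

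SE = √[1/(n·p0(1−p0)) + 1/(n·p1(1−p1))], with n = 128 per arm.

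At p0 = 0.50, SE = √(1/32.0 + 1/30.7) = 0.253, z = 0.405/0.253 = 1.60, and power = Φ(1.60 − 1.96) = 0.36. So 0.71 is not reproduced for a two-arm contrast even at 50%. Over all control rates the maximum is also about 0.36.

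A value near 0.71 does appear if the predictor is treated as standard normal, with z = √[N·p(1−p)·ln(OR)²·(1−R²)]. At p = 0.50 and R² = 0.40, z = √(256 × 0.25 × 0.164 × 0.60) = 2.51 and power = 0.709. The article gives no R², and the same formula returns about 0.71 at 40% (R² = 0.373), 30% (0.283), 25% (0.20) and 20% (0.06). The fit therefore does not identify the control rate used.

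**2. Control rate for HbA1c ≥6.5%.** The baseline proportion is zero. Under a constant hazard (an assumption), the Background range gives these 18-month incidences:

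- 10% over 10 years: 1 − 0.90^0.15 = 1.6%
- 40% over 10 years: 1 − 0.60^0.15 = 7.4%
- 10% in one year: 1 − 0.90^1.5 = 14.6%
- 40% in one year: 1 − 0.60^1.5 = 53.5%

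The last pairs the highest incidence with the shortest time. It does not fit the statement in Statistical analysis that onset is delayed by ten or more years.

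**3. Power at those rates.** The two-arm column uses the step 1 formula with both rejection tails counted. The last two columns use the standard-normal-predictor formula.

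| Control rate | ILSM rate | Events, both arms | Two-arm power | Normal predictor, R² = 0 | Normal predictor, R² = 0.40 |
|---|---|---|---|---|---|
| 50% | 40.0% | 115 | 0.36 | 0.90 | 0.71 |
| 15% | 10.5% | 33 | 0.19 | 0.64 | 0.43 |
| 10% | 6.9% | 22 | 0.14 | 0.49 | 0.33 |
| 5% | 3.4% | 11 | 0.10 | 0.29 | 0.19 |
| 2% | 1.3% | 4 | 0.07 | 0.15 | 0.10 |

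Worked line at 10%: SE = √(1/11.52 + 1/8.22) = 0.457, z = 0.887, power = Φ(−1.07) + Φ(−2.85) = 0.142 + 0.002 = 0.144.

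At a control rate of 15% or less, neither formula reaches 0.71, even with R² = 0, which sits badly with the covariate correlations the article describes.

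**The case against.** The strongest objection is that the article never says its calculation used 50% or 6.5%. A reader might infer that the plan fixes a 50% control rate. It does not: even odds is the natural reading of the wording, but no proportion is printed, and step 1 shows that 0.71 also arises at 20% to 40% with other values of R². A reader might also infer that 0.71 is claimed as power for T2DM incidence. The article does not say so: the parenthesis speaks of insulin resistance, which Table 3 ties to OGTT-2 h, and a lower HbA1c threshold such as a median split could make 50% reasonable. This stands, and it makes the conclusion conditional. It does not remove the problem, because the paragraph names HbA1c, gives one figure for both measures, and the document contains no other HbA1c cut-off.

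A further tempting inference is that a null diabetes result would be presented as evidence of no effect. The documents do not support that. The Discussion concedes that a long-term effect on T2DM incidence will be hard to show, and Statistical analysis already compares average changes in HbA1c, OGTT-2 h and BMI.

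Nor is the whole drop from 0.71 due to the control rate. The step from 0.71 to 0.36 is the separate fault that the figure does not reproduce for two arms. The control rate accounts for the step from 0.36 to 0.07–0.19. Finally, the cited incidence range is wide, and its extreme corner does reach 50%.

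**Conclusion.** The point holds in conditional form. The article states one power for two thresholded outcomes without a cut-off or control proportion for either. If the HbA1c threshold is the 6.5% in Table 3, the entry rule and the article's own view of diabetes onset rule out about 0.71: two-arm power is about 0.07 to 0.19 at control rates of 2% to 15%, with roughly 4 to 33 events in total. This rests on 128 per arm, a two-sided 0.05 test, a constant hazard, and time since GDM diagnosis standing in for time since baseline. Randomisation by town and dropout, which the power paragraph does not mention, would lower these values further.

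The low power does not depend on reading even odds as 50%, since two-arm power for this odds ratio and sample size is at most about 0.36 at any control rate.

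**What to change.** In the power paragraph of Study participants, give for each thresholded outcome the cut-off, the expected control proportion at the time point analysed and the resulting power, with treatment arm as a binary predictor. State that 0.71 does not apply to HbA1c ≥6.5%. If another HbA1c threshold was meant, name it and give its expected control proportion.

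Report HbA1c-defined T2DM as an estimate with a confidence interval, and rest conclusions on the continuous measures already listed in Statistical analysis. In the Discussion, limit the sentence that calls the sample size theoretically adequate for clinically meaningful differences to the outcomes for which that can be shown.

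These are wording changes, with no extra enrolment or data collection. The only cost is a less favourable stated power, most visibly for diabetes development.

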One study done in Australia reported limited and some success of the phone-based motivational interviewing program in the postpartum period for rural women with prior GDM in Australia [30]. The limited success of the phone-based intervention included that it was difficult to recruit a large proportion of potentially eligible women who may presume their lack of time to exercise with a new baby to care, no time to spend on their own needs or needing return to work early. Based on the literature, it is recommended that intervention builds on stronger theoretical foundation, such as Social Cognitive Theory [17, 20] and Behavioral Theory [23]. The ILSM program based on Social Cognitive Theory (SCT) [34] aims to increase participants’ self-efficacy by setting realistic and achievable goals, providing necessary skills, making individual action plans, improving self-regulation in maintaining and balancing health outcomes and health behaviors, via interactive group sessions and phone consultation provided by a local project field officer. The SCT was demonstrated success in increasing and even maintaining physical activity among individuals with T2DM in several intervention studies [17, 20, 35]. Our intervention is based on the evidence-based Tianjin Gestational Diabetes Mellitus Prevention Program (Tianjin-GDM-PP) [36] in China and results of our preliminary data [37] with rural culture and health care system tailoring.

There are some limitations to this proposed project, including its limited generalizability, self-report data, and limited geographical region only in Hunan Province. Long-term effect of ILSM program to decrease the incidence of T2DM in women with prior GDM will be difficult to show in this proposed project because of the limited project time. To reduce these limitations, we have included the sample size that is theoretically sufficient to detect meaningful clinical difference, used randomization techniques to maximize representation of the target population and increased follow up to 12 month post intervention given the grant funding duration and budget. We also have included several physiological outcomes to minimize self-report bias.

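### The stated power of about 0.71 cannot be obtained from the protocol's own inputs: for a two-arm comparison of 256 women at an odds ratio of 0.667, power is at most about 0.36 two-sided (0.49 one-sided)

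*Protocol article*

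**What the plan says.** The power paragraph of the protocol article (Methods, Study participants) describes a GPower 3.1 calculation for logistic regressions comparing ILSM with control on thresholds of OGTT-2 h and HbA1c. The effect is an odds ratio of 0.667, explained as "odds of insulin resistance above threshold in the ILSM groups versus the equal odds in the control group". The size is "a combined sample of *N* = 256", which agrees with the abstract: "A total sample of 256 participants will be recruited in the study". The type 1 error is .05, and the other covariates are taken to be fairly highly correlated. The result is that "the power of the test against null hypothesis of that the odds ratio is 1.0 is about 0.71". The paragraph gives no sidedness, no numerical control rate, no R² and no distribution for the predictor.

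The opening of the Methods assigns half of the towns in each county to each arm, with the town as the unit of randomisation. The limitations paragraph of the Discussion then says "we have included the sample size that is theoretically sufficient to detect meaningful clinical difference".

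**The concern.** The predictor being tested is study arm, which takes two values. An odds ratio of 0.667 from control odds of 1 is a difference of 50% versus 40%. With about 128 women per arm that is a modest contrast, and power of 0.71 looks far too high for it.

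This is the only quantitative support for the sample size in the article. If it is overstated, the sufficiency statement in the Discussion loses its basis. A reader who takes 0.71 at face value may also give a non-significant result more weight as evidence of no effect than the design allows.

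**Working it through.** **Inputs.** From the power paragraph: odds ratio 0.667, total N = 256, α = .05. Assumed: 128 women per arm (the article halves the towns, not the women). Control odds are read as 1, so the control rate is 0.50; other rates are scanned below. Sidedness is not stated, so both are shown.

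**1. Power for a two-level arm.**
- ILSM rate = 0.667 / (1 + 0.667) = 0.400.
- SE(log OR) = √[(1/(0.5 × 0.5) + 1/(0.4 × 0.6)) / 128] = √[(4 + 4.167) / 128] = 0.253.
- z = |ln 0.667| / 0.253 = 0.405 / 0.253 = 1.60.
- Two-sided power = Φ(1.60 − 1.96) = 0.36. One-sided power = Φ(1.60 − 1.645) = 0.48.

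A two-proportion formula gives 0.361 and 0.484. A simulation of the two-sided pooled test (400,000 runs) gives 0.368. The stated 0.71 is not reproduced.

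**2. Can the unstated inputs rescue 0.71?**

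*Control rate*, odds ratio held at 0.667, 128 per arm:

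| Control rate | Two-sided | One-sided |
|---|---|---|
| 0.10 | 0.14 | 0.23 |
| 0.20 | 0.23 | 0.33 |
| 0.30 | 0.29 | 0.41 |
| 0.40 | 0.34 | 0.46 |
| 0.50 | 0.36 | 0.48 |
| 0.60 | 0.36 | 0.48 |

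Over rates from 0.02 to 0.98 the maximum is 0.364 two-sided and 0.488 one-sided, both at a control rate of about 0.55.

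*Covariate correlation.* In this calculation the effective N is N × (1 − R²). At an illustrative R² of 0.4, z = 1.60 × √0.6 = 1.24, so power is 0.24 two-sided and 0.34 one-sided.

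*Town-level randomisation.* The article gives no design effect. Illustrative values of 1.1, 1.3, 1.5 and 2.0, each with R² = 0, give two-sided power of 0.33, 0.29, 0.26 and 0.20.

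None of these brings a two-level arm near 0.71.

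**3. What would give 0.71?**
- More women at the same odds ratio: about 313 per arm (626 in total) two-sided, or 240 per arm (480) one-sided.
- A standard-normal predictor in place of arm: z = 0.405 × √(256 × 0.25 × (1 − R²)). With R² = 0, z = 3.24 and power is 0.90. With R² = 0.4, z = 2.51 and power is 0.709. The odds ratio would then be per standard deviation of a continuous variable, which is not the trial's contrast.
- A standard-normal predictor with other values of the unstated inputs. With R² = 0, event rates of 0.15 and 0.20 give 0.638 and 0.736, which bracket 0.71. A one-sided test at an event rate of 0.50 with R² = 0.55 gives 0.701.
- Changed inputs: 256 per arm, one-sided, R² = 0.05 gives 0.716. Reading 0.667 as a risk ratio (0.50 versus 0.33) with R² = 0.15, two-sided, gives 0.705. The first contradicts the combined sample of 256, the second the stated odds ratio.

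**4. What 256 women can detect**, two-sided, 128 per arm, before covariate correlation, clustering and loss:
- Odds ratio from a 50% control rate: about 0.52 to 0.53 at 71% power and 0.48 to 0.49 at 80%, depending on the formula.
- Difference in mean change, in SD units, (1.96 + z_power) × √(2/128): (1.96 + 0.553) × 0.125 = 0.31 at 71% and (1.96 + 0.842) × 0.125 = 0.35 at 80%.

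**The case against.** The article is candid in two respects: it says that the assumptions behind such calculations are hard to verify, and it reports power below the customary 0.80. Its Statistical analysis section starts from differences in mean change, so the logistic figure does not describe the first comparison listed. The sufficiency statement is hedged and stands in a limitations paragraph. All of this is fair, and it bears on how much the error matters and on how the Discussion might be reworded. It does not make 0.71 obtainable. Nor is this a complaint that a condensed article omits detail: the figure fails for every value of the inputs left unstated, provided that arm has two levels.

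Three stronger readings are tempting, and the documents do not support them.

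- A reader might infer that 0.71 arose because arm was entered as a standard-normal predictor. That fits, but only with an R² of about 0.4 or another unstated value, and other routes also come close. The article does not say how the predictor was entered.
- A reader might infer that a 50% control rate conflicts with the Recruitment section, where "If HbA1c are within normal limits, the women will be recruited". That screen uses HbA1c. The odds ratio is written for insulin resistance above a threshold, and no OGTT-2 h threshold is given. The 10 to 40% in the Background is T2DM incidence, a different quantity. The result does not need this argument, because it holds at every control rate.
- A reader might take 0.36 as the trial's true power. It is an upper bound, with no covariate correlation, clustering or loss.

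**Conclusion.** The point holds. For ILSM versus control at an odds ratio of 0.667 with 256 women, power is at most about 0.36 two-sided or 0.49 one-sided, so 0.71 is about twice the best two-sided value. At that odds ratio the trial would miss the effect in almost two of three repetitions, even on the favourable assumptions.

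The conclusion rests on three things: arm analysed as a two-level variable, an approximately equal split of women, and the odds ratio and total N as printed. It does not depend on the control rate or on sidedness. How 0.71 was produced remains unknown.

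**What to change.** - In the power paragraph, replace 0.71 with power of at most about 0.36 two-sided for an odds ratio of 0.667 (50% versus 40%, 128 per arm), before covariate correlation, clustering and loss. Alternatively, give the detectable odds ratio: about 0.52 to 0.53 at 71% power and 0.48 to 0.49 at 80%, with the same caveats. Either way, state sidedness, control rate and R².
- Add the detectable difference for the mean-change comparison in the Statistical analysis section: about 0.31 SD at 71% power and 0.35 SD at 80%, before clustering and loss.
- In the Discussion, withdraw or qualify the statement that the sample size is sufficient.

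These are changes of wording. Enrolment, conduct and analysis stay as they are, and the cost is a less favourable stated power.
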